#### Early Start Denver Model (ESDM)

The Early Start Denver Model [30, 72] focuses on teaching inside children’s play and care activities, carried out within a joint activity structure [84]. Adults follow children’s leads into activities, embed teaching objectives inside the activity, use the play or child’s activity goal as the reward, and build targeted skills by applying ESDM teaching strategies from developmental science and ABA principles. ESDM uses a developmental curriculum that defines the skills to be taught in each area of development based on each child’s strengths and needs. Core features of ESDM include child preferred materials and activities, use of both developmental strategies and naturalistic ABA strategies, a focus on teaching developmentally appropriate, well-generalized functional skills, caregiver involvement, and a focus on positive social interactions embedded within everyday activities. ESDM uses decision trees to determine when and how to vary the primary, child-centered teaching practices to assure child progress. ESDM Fidelity Tools measure the quality of implementation (see below). Providers in regions randomized to ESDM will receive ESDM training as described below.

#### Usual early behavioral intervention (EBI)

Treatment as usual will vary based on the agency. However, a majority of CBAs use Discrete Trial Teaching (DTT) based on the Lovaas model [18]. DTT involves 10 components described in numerous research publications [85]: capturing child physical and visual attention, adult presentation of the stimuli and instruction (antecedent), child behavior, adult reinforcement, correction procedures, 3–5 s interstimulus interval between trials, behavior-specific praise, and data recording. The use of DTT and NDBI strategies will be measured across both groups (see below) to characterize interventions delivered. Providers in regions randomized to continue EBI will continue service as usual.

#### Caregiver participation

Most CBAs include caregivers in some way because caregiver involvement is required by most funders. Providers in the EBI group will work with parents as usual. Providers in the ESDM condition will receive training in ESDM caregiver coaching strategies and will be asked to conduct caregiver coaching in the strategies at least monthly. Providers in the ESDM group will have training in use of “Help is in Your Hands” (HIIYH; www.helpisinyourhands.org), an online program for parents that includes 4 modules focused on video examples of families using the strategies during daily routines. Modules cover: (1) Increasing Children’s Attention to People; (2) Increasing Children’s Communication; (3) Creating Joint Activity Routines; (4) ABCs of learning. HIIYH includes the core elements of ESDM which align with the 11 essential common elements shared across NDBIs.

#### CBA provider training

Working with our CBA partners, we determined that the best training approach for this trial would be using our experienced ESDM trainers to train CBA supervisors using a combination of synchronous and asynchronous methods. Trainer fidelity to the training model will be tracked. Technicians will receive asynchronous didactic trainings combined with coaching and feedback from their CBA supervisors (who will receive support from the project ESDM team).

#### Supervisor training

Training will begin with a series of asynchronous, interactive (e.g., quizzes and activities), web-based lessons, followed by online coaching of supervisors by the project team through video review of their ESDM implementation and both technician and caregiver coaching. Supervisors will be trained to fidelity in all aspects of the ESDM model: assessment, goal development, data collection and intervention strategies. They will be trained to fidelity in ESDM coaching strategies to be used with both caregivers and technicians. Supervisors will use on-line ESDM parent training videos, Help is in Your Hands (HIIYH), and the ESDM caregiver manual [86] for caregiver coaching. After reaching ESDM fidelity with their trainer, supervisors will attend several web-based monthly peer supervision meetings with other participating supervisors that will include ongoing fidelity checks, to assure their continued development of ESDM delivery skills (see Table 1).

**Table 1 Tab1:** Structure of the Early Start Denver Model (ESDM) Training Plan

Overview	Content & Format	Hours
ESDM Training for Supervisors		
What is the Early Start Denver Model	Introduction to ESDM theory and strategies, curriculum checklist, goal development, data collection. Format: asynchronous, interactive, video examples	2.5
ESDM Techniques and Strategies	Integrating joint activity routines. How to design and conduct an ESDM session; joint activity routines Format: asynchronous, interactive, video examples	2.5
Implementing Joint Activity Routines	Provider practices ESDM strategies (following child interest; sensitivity, themes etc.). Format: synchronous group video review	2^a^
Developing intervention plans	Using the ESDM Curriculum checklist for assessing learning strengths and needs. Using the checklist to create an intervention plan	3
Practice assessment and plan development	Practice conducting and coding curriculum checklist with feedback and developing goals until fidelity is met. Format: group video review, document review	2^a^
ESDM Coaching	Coaching during ESDM sessions until ESDM Fidelity is met. Format: Synchronous or video review	2^a^
Adult learning and providing coaching	Adult learning strategies to support successful coaching of technicians and caregivers in ESDM. Format: asynchronous	1
Practice with technician coaching	Using strategies to coach technicians	1^a^
Caregiver Coaching	Introduction to caregiver coaching strategies incorporating Help is in Your Hands Modules. Session preparation; collaborative coaching Format: asynchronous, interactive, video examples	7
Caregiver Coaching Feedback	Review of goal development and documentation; fidelity; Review of provider coaching caregiver sessions with ESDM trainer until fidelity is met. Format: Group video review	12^a^
Monthly Learning Collaborative	ESDM trainers host monthly learning collaborative for supervisors; Participants will provide case presentation, code ESDM fidelity and discuss challenges and successes	1 mo
ESDM Training for Technicians		
ESDM Introduction for Practice	Introduction to ESDM strategies and data collection. Format is asynchronous and includes interactive components and video examples	2
ESDM Intervention Training	Technicians will receive coaching and feedback from supervisors in accordance with the timing of training at their agency	varies
Just-in-Time (JIT) Micro Trainings	Access to JIT video modules (2–5 min) featuring ESDM examples matching age and goals of their current children. Modules can be viewed prior to treatment sessions to increase fidelity. Supervisors will assign at least 1 module per week for the first 8 weeks of training	varies

^a^additional coaching provided as needed to meet fidelity

#### Technician training

Technicians will complete asynchronous didactic training that includes an introduction to ESDM principles, strategies, and data collection. Supervisors will coach them in use of ESDM strategies using their agencies’ supervision model. Technicians will also view just-in-time (JIT) microlearning modules: specific 3 to 5-min lessons featuring a child of similar age, skill level and goals, just prior to an intervention session. Using JIT microlearning is an effective way to teach complex strategies [87, 88]. JIT learning provides immediate information when it is needed by delivering content in manageable units that fit technicians’ clinical schedules. Each JIT microlearning provides ideas for learning activities to teach a specific goal and brief information about how autistic children learn. A library of JIT videos will be made available and assigned to technicians by their supervisor. See Table 1 for the technician training plan.

#### Training materials

Supervisors will receive three ESDM manuals: the core treatment manual [72], a manual written for caregivers [86], and a manual on coaching caregivers in ESDM [86]. They will also receive access to HIIYH videos, caregiver coaching materials, a fidelity checklist for technicians, access to an ESDM goal bank, data collection tools, and access to JIT modules.

#### Fidelity to the ESDM training model

To assess fidelity to the ESDM training model, we will measure three training variables: (1) supervisor and technician completion of online training modules, JIT modules, and training activities will be tracked via the web-based training system; (2) supervisor participation in coaching and supervision activities, including receiving feedback and fidelity ratings from project staff for the curriculum assessment administration and scoring, goal development, ESDM implementation, caregiver coaching and technician coaching; and (3) trainer ESDM fidelity scores based on 25% of their ESDM Trainer coaching and supervision sessions coded by project staff. Supervisors who do not meet fidelity standards will receive supervision until they meet fidelity standards.

#### Treatment fidelity measures

We will assess supervisor ESDM fidelity at multiple levels: child skill assessment and goal development, ESDM strategy use, data practices, and coaching others. Supervisors and technicians will be coded on ESDM Strategy Use. Scoring sheets and the fidelity measures are available from the first author.

#### ESDM progress tracking and goal development

Supervisors will be scored on assessment and goal fidelity (curriculum checklist described below) on the ESDM Certification Rating System (CRS). Once using ESDM, they will submit curriculum checklists and objectives for each child enrolled in the study.

#### Caregiver and technician coaching

A modified version of the Coaching Practices Rating Scale (CPRS) [89] will evaluate supervisors’ fidelity to coaching strategies. Supervisors in both groups will submit one caregiver session and one technician supervision video per month for the duration of the study to examine fidelity. Each of the 13 fidelity items will be rated on a binary scale of present or absent, and these scores will be summed for a total of 13 possible points. Intraclass correlation coefficients in prior studies indicated high reliability: ICC = 0.92 (CI: 0.71–0.98).

#### ESDM strategy use fidelity

The ESDM Fidelity Checklist [72] will assess use of ESDM practices. The ESDM Fidelity Checklist consists of 13 items: (a) management of child attention; (b) ABC teaching format; (c) instructional techniques; (d) modulating child affect/arousal; (e) management of unwanted behavior; (f) use of turn-taking/dyadic engagement; (g) child motivation is optimized; (h) adult use of positive affect; (i) adult sensitivity and responsivity; (j) multiple varied communicative functions; (k) adult language; (l) joint activity and elaboration; and (m) transition between activities.

#### Use of NDBI strategies

To understand treatment differentiation between the ESDM and EBI groups we will code the use of NDBI strategies across groups. To examine differentiation between the interventions in a more valid and unbiased manner than simply using ESDM codes across conditions we will use the eight-item NDBI-Fi measure [90] developed to capture common elements across NDBI interventions. This measure has adequate reliability, sensitivity to change, and concurrent, convergent, and discriminative validity. We will use the total score and examine differences by strategy type, responsiveness, and directives, consistent with recent studies [91].

### Procedures and measures

Child and family level outcomes will be assessed at three time points by trained assessors naïve to intervention condition: Baseline (BL), 6 months, and 12 months post BL. Outcome data will be collected by administering a brief battery of measures via distance technology that includes interview and survey and assessments with caregivers and video recordings. All assessors will be experienced MA or PhD level clinicians and supervised by a licensed clinical psychologist with over 20 years of experience in assessing young autistic children. All data will be entered directly into secure computer systems. Interviewers and video coders will be naive to group status (ESDM or EBI). The primary outcome will be child social communication and language (caregiver report and observational coding). Secondary outcomes are: (1) adaptive behavior and cognitive gains, (2) progress toward goals; (3) quality of life; (3) caregiver use of NDBI strategies; (4) increases in caregiver competence. We will assess engagement of the identified treatment mechanisms: child social motivation and caregiver use of NDBI strategies. Measures, constructs, and timing are listed in Table 2. Commonly used measures are described briefly. Newer or less standard measures are described in more detail.

**Table 2 Tab2:** Assessments

Domain	Measure and description	Method	Timing		
			T1	T2	T3
**Characterization Measures**					
Demographics	Family Demographic Questionnaire	Caregiver Survey	X		
Devel Level	Devel. Profile -4th Ed, Cognitive	Caregiver Survey	X		
Treatment Type and Intensity	Ongoing Services Survey	Caregiver Interview	X	X	X
**Primary Outcomes**					
Language & Social Communication	Vineland Adaptive Behavior Scales-3 Communication Subscale	Caregiver Interview	X	X	X
	APPL	Direct Observation	X	X	X
**Secondary Outcomes**					
Adaptive Behavior	Vineland Adaptive Behavior Scales-3	Caregiver Interview	X	X	X
Quality of Life	CarerQoL; PEDSQL	Caregiver Survey	X	X	X
Caregiver Fidelity	NDBI-Fi	Direct Observation	X	X	X
Social Communication	Brief Observation of Social Change (BOSCC)	Direct Observation	X	X	X
Early Intervention Support and Processes	Family Outcomes Survey-Revised; Measure of Processes of Care	Self-Report		X	X
Potential Intervention Side Effects	Emotion Dysregulation Inventory-Young Children (EDI-YC) short form	Caregiver Survey	X	X	X
**Treatment Mechanisms**					
Social Motivation	PDDBI Social Approach Scale	Caregiver Survey	X	X	X
	JERI	Direct Observation	X	X	X
Caregiver Fidelity	NDBI-Fi	Direct Observation	X	X	X

T1 = baseline; T2 = 6 months; T3 = 12 months

Participant retention will be facilitated by frequent contact with the research team, gift cards for measure completion, birthday cards sent to children and assessment reports. If child participants leave the agency we will still attempt to obtain measures at each timepoint.

### Characterization measures

#### Treatment type and intensity

Caregivers will complete an interview regarding intervention services received during the study period. In addition, we will track the number of CBA-provided treatment hours and caregiver coaching attendance via agency records.

#### Cognitive level

The Developmental Profile-4 (DP-4) [92]. Cognitive Scale is a standardized caregiver interview measure that produces norm-referenced scores for the cognitive domain. Test–retest reliability for the Cognitive scale is 0.83; internal consistency 0.82 to 0.94. Construct validity was verified with comparison of established measures (cognitive scale = 0.57).

#### Primary child outcomes: social communication and language

We will examine the effect of ESDM training on children’s social-communication and language using observational coding and caregiver report.

The Assessment of Phase of Preschool Language (APPL) [93] operationalizes research-based language development stages [94]. Language phases are derived from spoken language or augmentative communication systems and standardized assessments. The APPL characterizes expressive language domains: phonology, vocabulary, grammar, and pragmatics. For each domain, the APPL outlines the range of demonstrated skills that could meet criteria for each phase: Phase 1: Preverbal; Phase 2: First Words; Phase 3: Word Combinations, Phase 4: Sentences, or Phase 5: Complex Language. The APPL has strong interrater reliability and good construct validity A Language samples will be obtained from transcriptions of child-caregiver interactions recorded at each timepoint (see video collection). The APPL has been used to examine change in language level in multiple autism studies.

#### Vineland communication domain

The Vineland Adaptive Behavior Scales-3 (VABS-3) [95] consists of four domains of adaptive behavior: communication, daily living skills, socialization, and motor skills. It has been validated with children with developmental disabilities The scales yield normative standard scores (M = 100; SD = 15) that can be used for comparison across groups. The communication domain will be used to examine overall change in communication in the natural environment. The Vineland Interview edition will be used to obtain parent report of adaptive skills.

#### Secondary outcomes

##### Adaptive behavior

*Vineland Adaptive Behavior Scales-3* (VABS-3) [95] domains of adaptive behavior: daily living skills, socialization, and motor skills will be examined as secondary outcomes.

##### Caregiver and child quality of life

The CarerQoL [96]assesses perceived caregiver quality of life across seven dimensions. The Pediatric Quality of Life Inventory (PedsQL) [97] assesses children’s quality of life across four domains based on caregiver report and has been validated in an autism population [98].

##### Brief observation of social communication change

(BOSCC; [99]. The BOSCC consists of 15 items coded based on video observations on a 6-point scale ranging from 0 (the characteristic is not present) to 5 (the characteristic is present and it significantly impairs functioning). Thus, higher scores indicate more autism characteristics. Items 1–8 focus on Social Communication (SC), while items 9–12 capture Restricted and Repetitive Behaviors (RRBs). The BOSCC results in SC (i.e., eye contact, facial expressions, gestures, vocalizations, integration of vocal and non-vocal communication, frequency/function of social overtures, frequency/quality of social responses, engagement in activities/interaction, and play with objects) and RRB domain totals (unusual sensory interests, hand/finger or other complex mannerisms, and unusually repetitive interests/stereotyped behaviors). The Core total combines the SC and RRB scores. We will not be targeting autistic characteristics in our project. We will include the BOSCC as a secondary measure of social communication to facilitate comparison across studies.

##### Early intervention support and processes

The *Family Outcomes Survey-Revised* (FOS-R) [100] is a 41-item measure uses a 5-item Likert scale to assess parents’ perceived strengths and needs as they relate to the early intervention support they receive. The FOS-R has good internal consistency in English (subscales ranging from 0.73 to0.95 for Cronbach’s alpha). [100] The *Measure of Processes of Care—20* (MPOC—20) [101] measures how family-centered parents perceive their child’s intervention services. The 20-item scale asks parents to rate how much people who work with their child (a) enable partnership, (b) provide general information, (c) provide specific information about their child, (d) coordinate comprehensive care for the child and family, and (e) are respectful and supportive. The scale has good internal consistency with coefficients ranging from 0.83 to 0.90 [101].

##### Intervention side effects & harm

*Emotion Dysregulation Inventory-Young Children* (EDI-YC) [102] short form measures emotion dysregulation with two scales, reactivity and dysphoria. Reactivity is characterized by rapidly escalating, intense, labile negative affect and difficulty downregulating that affect. Dysphoria is characterized by poor up regulation of positive emotion. This 14-item scale has been used with children on the autism spectrum. The measure has good validity and is supported by expert review. If children have > 1sd of change in this measure over time or providers or parents report regression the research team and data safety and monitoring board will assess for discontinuing or modifying the intervention and/or study participation.

#### Treatment mechanisms variables

##### Social motivation and caregiver NDBI fidelity

Social motivation will be measured in two ways and those assessments will be used to examine proximal and distal changes to the intervention mechanism and its role as a moderator.

*Pervasive Developmental Disorder Behavior Inventory (PDDBI)* [103] examines characteristics of autism in children between 18 months and 12.5 years through caregiver reports. It has high internal consistency (0.84—0.97), inter-rater reliability (ICC = 0.75—0.93), and good construct validity. The Social Approach subscale will provide a distal measures of social motivation (treatment mechanism) and includes 36 items representing all three behavioral manifestations of social motivation. Studies using the Social Approach subscale report good consistency (α = 0.94) and test–retest reliability of 0.93 [104, 105].

Joint Engagement Rating Inventory (JERI) [106] will be a proximal, objectively rated measure of child social motivation during adult/child interactions. The JERI is widely used to examine child behavior in autism studies and has high validity and reliability. One score per code will be assigned to each Communication Play Protocol observation (see below) and averaged across the 3 activities for analyses.

##### Caregiver NDBI fidelity

Caregiver-child interaction videos (see below) will be coded using the NDBI-Fi Checklist (see Fidelity measures and video collection).

#### Video data collection

Video data will be collected for outcomes at three time points using the Communication Play Protocol (CPP) [107]. The CPP produces video records of three 5-min semi-structured scenes that focus on requesting, social interacting, and shared commenting. We will collect two CPP videos at each time point, one with the caregiver and one with a provider that does not know the child and is naïve to condition. Video data will be coded using the (1) APPL for children language outcomes; (2) JERI to assess social motivation; and (3) and NDBI-Fi to examine caregiver use of ESDM/NDBI strategies.

##### Video coding procedures

Trained coders naïve to group, timepoint, and study aims will code video measures to avoid bias. Each coder will be trained in one scoring system to reliability (80% agreement over 3 videos). For each measure, a random sample of 20% of sessions will be double coded for inter-rater reliability throughout coding. If agreement drops below 80%, training will be provided until agreement is achieved.

#### Analytic plan

In this trial, there are several levels of clustering: repeated observations are nested within the child/caregiver, the child/caregiver is nested within the team, teams are nested within the region, and regions are nested within CBAs. Therefore, we will use a modeling strategy that includes random intercepts for region and/or CBA, team, and random child/caregiver effects (intercept, slopes, as appropriate). All primary analyses will be conducted on an intent-to-treat basis using a generalized linear mixed-effects models framework [103], which can accommodate continuous, binary, and count outcomes through an appropriate choice of link function. Preliminary analyses will involve examining the outcomes and covariates to verify their appropriateness, identifying patterns of missing data, and conducting a multivariate outlier analysis. Model validation will be carried out using both analytical and graphical techniques to check core assumptions such as linearity, distribution, and homoscedasticity. Transformations of outcome variables will be considered if suggested by the model validation analyses. All analyses will include available relevant biological variables, including child or caregiver sex and age and baseline characteristics if there is any evidence of randomization imbalance in them. Randomization should produce intervention and control groups that are comparable and balanced. As a first-order check on confounding, we will examine the success of randomization by comparing baseline characteristics of children, caregivers, and providers assigned to the two study arms. Where clinically significant differences are apparent, child-, caregiver-, and provider-specific covariates will be added to the statistical models as fixed predictors to examine whether the intervention effect is robust in their presence.

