**Fig. 2 Fig2:**
[figure not shown]
CONSORT flowchart for recruitment of community-based agencies and participants (projected)

CBAs throughout the US will be recruited, through emails, presentations at conferences and social media, to increase diversity and generalizability. Interested CBA leaders will be invited to meet with the study team. Those CBAs expressing interest and meeting inclusion criteria (see below) will be enrolled in the study. The randomization unit is the region. Within each CBA, regions will be randomized to either receive training in ESDM or continue usual early behavioral intervention (EBI). We chose to randomize at the region level to prevent potential contamination across providers and children, as our community partners indicated that children often receive treatment from multiple providers within a region. Using covariate constrained randomization, regions will be randomized so each CBA is represented in both ESDM and EBI. The variables considered in the constrained randomization include insurance mix (proportion of clients with Medicaid < 0.5 or ≥ 0.5) and size (number of autistic children under age 5 < 20 or ≥ 20). The study statistician will generate the randomization scheme before the enrollment of the first CBA and reveal the random assignments to the appropriate members of the study team. Members of the study team involved in assessments will remain unaware of the intervention assignment.

A cascading recruitment strategy will be used to first recruit agencies and then supervisors within participating regions. Supervisors will then recruit children and families and the technicians working with those children. Recruitment at each level will be facilitated through videos and handouts explaining the study and the processes. The research team will present to interested supervisors at team meetings. Supervisors will receive a handout and link to a video to share with technicians and families. Interested technicians and families will set up a time to talk with the research team about the study to determine interest.

This study was approved by the institutional review board at the University of California, Davis, protocol number 203076–2. This study is funded by the National Institute of Mental Health (NIMH; R01MH131703 and supported by the MIND Institute Intellectual and Developmental Disabilities Research Center (IDDRC) funded by the National Institute of Child Health and Human Development (NICHD; P50 HD103526).

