#### Primary and secondary outcomes

The analytic approach for each primary and secondary outcome measure will follow the same general model-building strategy. For outcomes assessed at baseline, 6 months, and 12 months, the models will include fixed effects for time (baseline, 6-, and 12-months), group, and their interaction, as well as covariates (e.g., child/caregiver sex, age, etc.) and random effects for child/caregiver, team, or region to account for clustering. The interaction between time and group will directly test the hypothesis that participants in the ESDM group show greater improvement than those in the EBI group. In all models, we will consider adding relevant covariates related to child/caregiver or provider-level characteristics if randomization at the region level did not ensure comparability between the two groups [108].

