#### Power considerations

Given that the proposed analyses for primary outcomes will employ mixed effects modeling of clustered data to assess differences in changes from baseline between treatment groups, power analyses were conducted using Monte Carlo simulations of multi-level models in SAS (SAS Institute Inc., Cary, NC). Expected fixed effect values for effects of interest (e.g., treatment group by time interactions) were obtained from prior research on ESDM treatments and developmental change [109]. We assumed a range of plausible intraclass correlation coefficient (ICC) values for the random effects of child/caregiver dyad (0.3 to 0.5), team (0.1 to 0.25), and region (0.05 to 0.1) based on previous community intervention studies and pilot data and accounted for a 10% dropout rate. We used a type I error level of 5%.

Under each scenario, our proposed sample size of 300 children/caregivers, 100 teams, and 20 centers would provide at least 80% power to detect a standardized improvement in children’s social communication and language of *d* = 0.6. We assumed that 10% of children would not contribute any data; however, the participants who dropped out would have provided some data and will contribute to the analyses. Therefore, our calculations are conservative.

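### Region and team enter the primary model only as random intercepts, which cancel from the tested difference in change; type I error exceeds 5% if improvement varies by region or team

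*Protocol article*

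**What the plan says.** Under Design & Randomization the region is the randomised unit, and each community-based agency (CBA) has regions in both arms. Region was chosen to limit contamination, because "children often receive treatment from multiple providers within a region".

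The Analytic plan lists the nesting (visits in child, child in team, team in region, region in CBA) and then specifies "random intercepts for region and/or CBA, team, and random child/caregiver effects (intercept, slopes, as appropriate". Slopes appear only in the bracket attached to the child/caregiver effects.

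Under Primary and secondary outcomes, time is baseline, 6 and 12 months, and the test is named: "The interaction between time and group will directly test the hypothesis that participants in the ESDM group show greater improvement". The same section describes the clustering terms as "random effects for child/caregiver, team, or region to account for clustering".

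No cluster-by-time random effect and no cluster-robust variance is stated anywhere in the article.

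**The concern.** The tested quantity is a within-child contrast: change from baseline, compared between arms. A random intercept for region or team shifts all visits of its children by the same amount, so it drops out when one visit is subtracted from another. The variance that matters for this test is how much regions and teams differ in improvement, and the stated model has no term for it.

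There is reason to expect such differences. Usual care is said to vary by agency, treatment intensity varies, and supervisors coach their own technicians under their agency's supervision model. These influences act during follow-up, so they affect change and not only level.

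At stake are the primary p-value and confidence interval. If cluster variance in change is present and omitted, a null effect of ESDM is declared positive more often than the nominal rate.

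**Working it through.** **Inputs from the article.** 300 children, 100 teams, about 3 children per team, 1:1 allocation, 5% type I error (two-sided assumed), 10% dropout, d = 0.6. A mean of 5 supervisors per region gives 100/5 = 20 regions of 15 children. But 20 CBAs with at least 2 regions each gives at least 40 regions, of 300/40 = 7.5 children. Both are shown.

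**Input not in the article.** The region and team ICCs of change. Power considerations gives "team (0.1 to 0.25), and region (0.05 to 0.1) based on previous community intervention studies", but does not say that these apply to change. They are borrowed here as the upper part of an assumed range that starts at zero.

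**Step 1: the stated power figure.** The article says the sample "would provide at least 80% power to detect a standardized improvement in" the primary outcome of d = 0.6. Suppose d is in SD-of-change units, there are 10 regions, 50 teams and 135 analysed children per arm, and cluster variance enters the contrast. Then

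Var = 2 × [ρ_region/10 + ρ_team/50 + (1 − ρ_region − ρ_team)/135], tested on 18 df.

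- 0.05/0.10: Var = 2 × (0.0050 + 0.0020 + 0.0063) = 0.0266, SE 0.163, 0.6/SE = 3.68, power 93.5%.
- 0.10/0.25: Var = 2 × (0.0100 + 0.0050 + 0.0048) = 0.0396, SE 0.199, 0.6/SE = 3.01, power 81.3%.

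So at least 80% is met on this reading.

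**Step 2: cancellation.** Write the score as Y = fixed part + region + team + child + error. For one child, Y(12 months) − Y(baseline) removes the region, team and child intercepts and leaves the fixed part and error. With a random intercept only, children's changes are therefore treated as independent. A child slope adds variance between children but still treats them as independent within a region.

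**Step 3: size of the test when cluster variance in change is ignored.** With m children per region and 3 per team,

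design effect DE = 1 + (m − 1) × ρ_region + 2 × ρ_team

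type I error = 2 × [1 − Φ(1.96/√DE)]

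| ICC of change, region/team | DE, 20 regions (m = 15) | Type I error | DE, 40 regions (m = 7.5) | Type I error |
|---|---|---|---|---|
| 0/0 | 1.00 | 5.0% | 1.00 | 5.0% |
| 0.01/0 | 1.14 | 6.6% | 1.065 | 5.8% |
| 0.02/0.02 | 1.32 | 8.8% | 1.17 | 7.0% |
| 0.05/0.10 | 1.90 | 15.5% | 1.525 | 11.2% |
| 0.10/0.25 | 2.90 | 25.0% | 2.15 | 18.1% |

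**Step 4: simulation under the null** (20 regions × 5 teams × 3 children × 3 visits, 5,000 runs per scenario). With cluster effects constant over time, rejection was 4.8–5.0%. With child/team/region ICCs of 0.3/0.1/0.05 and 10, 20 or 50% of the region and team variance specific to a visit, the 12-month contrast rejected in 7.1, 8.1 and 14.2% of runs. Using a child-level change variance, as a child slope would, gave 7.0, 8.2 and 14.0%, so slopes do not repair it. With region- and team-by-time effects, or a region-level analysis of change on 18 df, rejection was 4.4–5.3%.

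Random-intercept mixed-model fits at the same ICCs agreed: 41/268 = 15.3% with half the cluster variance visit-specific and 9/250 = 3.6% with none. Some fits gave convergence warnings; the formula and the balanced simulation do not depend on them.

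**The case against.** The strongest reply is that inflation is not established. It needs nonzero region or team variance in change, which the article does not quantify. With time-constant cluster effects the planned test is valid. The larger figures rest on ICCs that read most naturally as shares of score variance, and on 20 regions, which is not settled. All of this stands, which is why the size is given as a range starting at 5%.

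A second reply is that a condensed article may leave random-effects detail to the analysis plan, and that the outcomes section says random effects without limiting them to intercepts. This stands for degrees-of-freedom methods and covariance structure. It does not answer the main point: the article does say which levels get intercepts and which get slopes, and that choice leaves the randomised unit out of the tested contrast.

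A reader might infer that the power section exposes the fault, since an intercept-only model would detect 0.19–0.36 SD while d = 0.6 fits a clustered contrast. The documents do not support this. The first range is in score-SD units and the clustered figure is in change-SD units. At least 80% power holds under both readings, and the SD behind d is not defined.

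A reader might also make much of the wording that lets region be left out. Under the stated model a region intercept cancels anyway, so this is a secondary wording fault. The joining word in the outcomes section may only mean whichever levels apply to a given outcome.

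**Conclusion.** The concern holds conditionally. As written, the model carries no region- or team-level variation in improvement into the standard error of the primary test, although region is the randomised unit and the text on delivery makes such variation plausible. If it exists, type I error exceeds 5%: modestly at small values (6.6% with 20 regions or 5.8% with 40, at 0.01/0) and seriously at the borrowed ICCs (15.5–25% with 20 regions, 11.2–18.1% with 40).

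Confidence is high for the cancellation and low for the size. The cancellation is exact for a linear mixed model with complete visits. The size rests on assumed ICCs of change, a balanced layout and a two-sided test. The power statement is not shown to be wrong.

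**What to change.** State that region and team are always in the primary model and that their random effects act on change. Either of two forms does this:

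- add region-by-time and team-by-time random effects to the planned model; or
- model the 6- and 12-month scores with baseline as a covariate and random intercepts for region and team, and test the group effect on those scores rather than its interaction with time.

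Base inference on the number of regions, and state that number. Making the region intercept mandatory is not enough on its own, because it still cancels from the interaction.

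Replace the optional wording in both sections so that the randomised unit cannot be left out. CBA may be kept as an additional term but cannot stand in for region, since each CBA is in both arms.

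The cost is wording only, with no new data. Standard errors widen if cluster variance in change exists. If d = 0.6 is in SD-of-change units, power with 20 regions remains about 81–94% at the borrowed ICCs.
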